#### 5.12.7 Unscheduled Clinical Follow-up

If a subject comes for an unscheduled visit with the need of a (re-)intervention (e.g. based on present symptoms, diagnostic measures) the following assessments should be done **prior** to the (re-)intervention:

- Documentation of adverse events which might have occurred since last visit and the actual status of the adverse events
- Documentation on concomitant medication in case medication changed since last visit and the actual status of the concomitant medication.

- Ischemia should be documented by ECG, stress ECG, cardiac biomarkers or fractional flow reserve (FFR).
- Assessment of the ischemic/angina status (CCS, Braunwald or silent ischemia).

#### Unscheduled Angiographic follow-up

Any unplanned angiography and revascularization must be followed by a full clinical evaluation. The required data are to be entered into the CRF. All films must be sent to the angiographic core laboratory for review.

- If subjects undergo a clinically driven angiography within 3 or 9 months post procedure, having no re-intervention of the target lesion(s) they must return for the angiographic follow up visit at 6 and respectively, 12 months post procedure. Subjects shall not have the IVUS or the OCT examination during a clinically driven angiography within 3 months post procedure
- If subjects undergo a clinically driven angiography between 3-6 months post procedure (or at 9-12 months, respectively), this will be considered as the 6 months, respectively 12 months follow up angiography. IVUS and the OCT examination shall be done during the clinically driven angiography between 3-6 months or 9-12 months post procedure.
- If subjects have a re-intervention for in-scaffold restenosis at any time prior to the 6 months or prior to the 12 months follow up visit, they will not have an additional angiography at the 6 months or at the 12 months follow up visit respectively. This also applies for treatment of an acute or sub-acute thrombotic occlusion of the target lesion(s). Subjects should have the IVUS and the OCT examination during the time of re-intervention.
- However, if a subject has two target vessels treated with the study scaffold, whereof only one had a re-intervention, they must return for the repeat angiography at the 6 months and 12 months follow up visit. IVUS and the OCT examination shall be done during the repeat angiography.

### 5.13 Withdrawals / Study Exit

Early termination of study participation may apply for a study subject in any of the following situations:

- Screening failure
- Withdrawal of informed consent
- Not implanted, after the 1 month visit
- Lost to follow-up
- Death

The subject is free to withdraw its written informed consent at any time. The reason for withdrawal/discontinuation should, if available, be documented in the subjects' medical file and in the eCRF. When a subject withdraws or is withdrawn from the clinical investigation, a final clinical evaluation should be performed, documented in the medical record and in the eCRF.

A subject is not considered lost to follow up until the full 3 years have elapsed. The investigator should try to contact the subject at every follow-up until clinical investigation ends. At least 3 phone attempts and 1 attempt by registered mail should be performed for each missed visit. These attempts should be documented in the subject's medical records.

### 5.14 Study completion/Termination

Subject will terminate study participation when all protocol-required study procedures and follow-ups have been completed.

## 6. ADVERSE EVENTS

During the course of this clinical investigation adverse events might occur. For all (provisionally) enrolled subjects, adverse event information will be collected throughout the clinical investigation in the eCRF by the investigator or designee. Any adverse event will be followed until study end.

### 6.1 Adverse Event Definition and Classification

Adverse Events are defined and classified in this section according to the current version of ISO 14155.

[figure not shown]

Figure 1: Adverse Event classification

### AE – Adverse Event:

ISO 14155: any untoward medical occurrence, unintended disease or injury, or untoward clinical signs (including abnormal laboratory findings) in subjects, users or other persons, whether or not related to the investigational medical device.

Please note: Any current condition that is recorded as a pre-existing condition either in the medical history of physical examination section, is not an AE unless there is a change in nature, severity, or degree of incidence.

### ADE – Adverse Device Effect:

ISO 14155: *adverse event* related to the use of an investigational medical device

- This definition includes adverse events resulting from insufficient or inadequate instructions for use, deployment, implantation, installation, or operation, or any malfunction of the investigational medical device.
- This definition includes any event resulting from use error or from intentional misuse of the investigational medical device.

**SAE – Serious Adverse Event:**

ISO 14155: *adverse event* that

- a) led to death,
- b) led to serious deterioration in the health of the subjects, that either resulted in
  - 1) a life-threatening illness or injury, or
  - 2) a permanent impairment of a body structure or a body function, including chronic disease or
  - 3) in-subject or prolonged hospitalization, or
  - 4) medical or surgical intervention to prevent life-threatening illness or injury or permanent impairment to a body structure or a body function,
- c) led to foetal distress, foetal death or a congenital abnormality or birth defect

Please note: Planned hospitalization for a pre-existing condition, or a procedure required by the CIP, without serious deterioration in health, is not considered a serious adverse event.

**SADE – Serious Adverse Device Effect:**

ISO 14155: *adverse device effect* that has resulted in any of the consequences characteristic of a serious adverse event.

**USADE – Unanticipated Serious Device Effect:**

ISO 14155: Unanticipated adverse device effect means any serious adverse device effect which by its nature, incidence, severity or outcome has not been identified in the current version of the risk analysis report.

**Device Deficiencies**

ISO14155: Inadequacy of a medical device with respect to its identity, quality, reliability, safety or performance. Device deficiencies include malfunctions, use errors and inadequate labelling.

### **Serious Device Deficiencies**

Serious device deficiencies are device deficiencies that turned out to be serious because

- suitable action had not been taken;
- intervention had not been made; or
- if circumstances had been less fortunate.

### **Adverse Event Reporting**

Adverse event reporting will start once the patient is provisionally enrolled. Only events related to any study specific invasive procedures (e.g. blood draw) will be reported for this study population. For subjects considered fully enrolled in the study, all events will be reported.

### **According to ISO14155, the investigator shall:**

- Record every AE and observed device deficiency, together with an assessment
- Report to the sponsor, without unjustified delay, all SAEs and device deficiencies that could have led to an SADE; this information shall be promptly followed by detailed written reports
- Return the device in case of a device deficiency to the sponsor for further assessments.
- Report to the institutional review board (IRB)/independent ethic committee (IEC) SAEs and device deficiencies that could have led to an SADE, if required by national regulations or IRB/IEC
- Report to regulatory authorities SAE and device deficiencies that could have led to an SADE, as required by national regulations.
- Supply the sponsor, upon sponsor's request, with any additional information related to the safety reporting of a particular event.

Adverse events classified to be "serious" and/or with a relation to the investigational device have to be reported to BIOTRONIK as soon as possible after awareness by the investigator or by the investigator's designee without any unjustified delay.

Reporting should be done using the “Adverse Event or Device Deficiency Form” in the CRF. This report should deliver any information available at the time of reporting. Effort has to be made to collect as much information as possible during initial reporting. Follow-up information has to be delivered as fast as possible to ensure timely completion of the report.

The investigator is obliged to provide copies of blinded source documents from the patients’ medical records, for all SAEs and ADEs, as requested by BIOTRONIK, as well as any additional information required in relation to the event. Angiographic films and technical worksheets must be sent to BIOTRONIK.

**According to MEDDEV 2.7/3 revision 3, May 2015, the Sponsor shall:**

Report to the Notified Competent Authorities (NCAs) where the clinical investigation has commenced:

- for all reportable events as described in **MEDDEV 2.7/3 revision 3**, section 4 which indicate an imminent risk of death, serious injury, or serious illness and that requires prompt remedial action for other patients/subjects, users or other persons or a new finding to it: immediately, but not later than 2 calendar days after awareness by sponsor of a new reportable event or of new information in relation with an already reported event.
- any other reportable events as described in **MEDDEV 2.7/3 revision 3**, section 4 or a new finding/update to it: immediately, but not later than 7 calendar days following the date of awareness by the sponsor of the new reportable event or of new information in relation with an already reported event.

Primary contact for reporting Serious Adverse Events:

Safety Reporting

BIOTRONIK AG

BIOMAG-I, version 3.0, 16Apr2021

Page 91/ 156

Based on A06 TMP 150362 EN 01 A

Vascular Intervention

[name], [name], Switzerland

[contact]

[contact]

[contact]

## 7. STATISTICAL ANALYSIS

This chapter gives an overview on the planned analysis of the data. The final description of analysis will be laid down in a Statistical Analysis Plan (SAP) prior to analysis of the data.

### 7.1 Study Populations

Primary and secondary endpoint analysis will be conducted on the following pre-defined analysis populations:

- Intent-to-treat population (primary analysis)
  - Subjects for whom an investigational scaffold enters the guide catheter following the diagnostic angiography, regardless of whether the investigational scaffold is implanted in the intended location or not.
  - Subjects who received an investigational scaffold and who are later determined not to meet study eligibility criteria or who have CIP violations.

*Note:* Subjects, for whom DREAMS 3G entered the guiding catheter following the diagnostic angiography but who are not implanted (e.g. a different device had to be implanted) will be followed up until 1 month. Only baseline characteristics, device and procedure success, and safety up to 1 month will be reported for them.

- Per protocol population
  - Subjects implanted with the investigational scaffold at the intended location and who do not deviate from any relevant eligibility criteria and complete the study follow-up requirements without any relevant CIP violation.

## 7.2 Determination of Sample Size

The BIOMAG-I trial will assess non-inferiority of the 6-month in-scaffold late lumen loss for the DREAMS 3G scaffold vs. in-scaffold late lumen loss of a historical control from clinical trials with PLLA scaffolds as well as metallic scaffolds.

### 1-Primary endpoint in-scaffold late lumen loss at 6-month:

A weighted mean of 0.29mm for in-scaffold late lumen loss and a weighted pooled SD of 0.34mm were calculated based on below 6-month data from listed clinical trials.

|                  | In-scaffold LLL (mm)
@ 6 months
Mean (SD) | N | Publication   |
|------------------|----------------------------------------------------------|----------|----------------------|
| ABSORB    | 0.44(0.35)                                               | 26       | Ormiston 2008 (46)   |
| ABSORB    | 0.19(0.18)                                               | 41       | Serruys 2010 (37)    |
| Desolve   | 0.19(0.19)                                               | 14       | Verheye 2014 (94)    |
| Magmaris  | 0.44(0.36)                                               | 113      | Haude 2016 (11)      |
| Desolve   | 0.20(0.32)                                               | 113      | Abizaid 2016 (70)    |
| Fantom II | 0.25(0.4)                                                | 100      | Chevalier 2019 (102) |

For the DREAMS 3G the in-scaffold late lumen loss is thus estimated to be 0.29 mm.

The null and alternative hypotheses for non-inferiority testing of the primary endpoint are formulated as the following:

$$H_0: \mu_1 \geq \mu_{01} + \Delta$$

$$H_a: \mu_1 < \mu_{01} + \Delta$$

Here,  $\mu_1$  is the mean in-scaffold LLL of DREAMS 3G at 6 months after index procedure,  $\mu_{01}$  is the historical control value derived as the weighted mean of in-scaffold LLL at 6

months obtained from the literature review ( $\mu_{01} = 0.29 \text{ mm}$ ), and  $\Delta$  is the prespecified non-inferiority margin ( $\Delta = 0.145 \text{ mm}$ ).

Substituting the absolute values, the hypotheses can be simplified to the following:

$$H_0: \mu_1 \geq 0.435 \text{ mm}$$

$$H_a: \mu_1 < 0.435 \text{ mm}$$

The sample size calculation is made with:

|                               |       |
|-------------------------------|-------|
| Power:                        | 0.95  |
| Alpha:                        | 0.025 |
| NIM (Non-Inferiority Margin): | 0.145 |
| S (Standard Deviation):       | 0.34  |
| Dropout rate:                 | 15%   |

Rejection of the null hypothesis will mean that in-scaffold LLL of DREAMS 3G is non inferior to the historical control at 6-month. A total of 88 subjects enrolled (74 subjects plus 15% dropout) will have 95% power to reject the above null hypothesis in favor of the alternative assumptions.

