### 4.2 Hypothesis

As a primary endpoint, the BIOMAG-I trial will assess non-inferiority of the 6-month in-scaffold late lumen loss of the DREAMS 3G scaffold vs. in-scaffold late lumen loss of a historical control from clinical trials with PLLA scaffolds as well as metallic scaffolds.

| Scaffold | 6 months
In-scaffold LLL (mm)
Mean ( SD) | N | Publication |
|-----------------|---------------------------------------------------------|----------|--------------------|
| ABSORB   | 0.44(0.35)                                              | 26       | Ormiston 2008 (46) |
| ABSORB   | 0.19(0.18)                                              | 41       | Serruys 2010 (37)  |
| Desolve  | 0.19(0.19)                                              | 14       | Verheye 2014 (94)  |
| Magmaris | 0.44(0.36)                                              | 113      | Haude 2016 (11)    |
| Desolve  | 0.20(0.32)                                              | 113      | Abizaid 2016 (70)  |

| Scaffold  | 6 months             | N   | Publication          |
|-----------|----------------------|-----|----------------------|
|           | In-scaffold LLL (mm) |     |                      |
|           | Mean ( SD)           |     |                      |
| Fantom II | 0.25(0.4)            | 100 | Chevalier 2019 (102) |

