### Secondary endpoint in-scaffold late lumen loss at 12-month:

A weighted mean of 0.33 mm for in-scaffold late lumen loss and a weighted pooled SD of 0.35 mm were calculated based on the 12 month results of below listed clinical trials.

| Scaffold          | In scaffold LLL (mm)
@ 12 months
Mean (SD)     | N        | Publication             |
|-------------------|------------------------------------------------------|----------|-------------------------|
| Absorb            | 0.27 (0.32)                                          | 56       | Serruys 2011 (38)       |
| Magmaris          | 0.39 (0.34)                                          | 99       | Haude 2018 (21)         |
| Fantom II         | 0.29 (0.36)                                          | 31       | Gomez Lara 2011 (124)   |
| Mirage Vs. Absorb | 0.37 (IQR: 0.08 to 0.72)
0.23 (IQR: 0.15 to 0.37) | 35
27 | Tenekecioglu 2017 (125) |

For the DREAMS 3G the in-scaffold late lumen loss is estimated to be 0.33 mm.

The null and alternative hypotheses for non-inferiority testing of the powered secondary are formulated as the following:

$$H_0: \mu_2 \geq \mu_{02} + \Delta$$

$$H_a: \mu_2 < \mu_{02} + \Delta$$

Here,  $\mu_2$  is the mean in-scaffold LLL of DREAMS 3G at 12 months after index procedure,  $\mu_{02}$  is the historical control value derived as the weighted mean of in-scaffold LLL at 12 months obtained from the literature review ( $\mu_{02} = 0.33 \text{ mm}$ ), and  $\Delta$  is the prespecified non-inferiority margin ( $\Delta = 0.145 \text{ mm}$ ).

Substituting the absolute values, the hypotheses can be simplified to the following:

$$H_0: \mu_2 \geq 0.475 \text{ mm}$$

$$H_a: \mu_2 < 0.475 \text{ mm}$$

The sample size calculation is made with:

|                               |       |
|-------------------------------|-------|
| Power:                        | 0.95  |
| Alpha:                        | 0.025 |
| NIM (Non-Inferiority Margin): | 0.145 |
| S (Standard Deviation):       | 0.35  |
| Dropout rate:                 | 25%   |

Rejection of the null hypothesis will mean that in-scaffold LLL of DREAMS 3G is non inferior to the historical control at 12-month. A total of 104 subjects enrolled (78 subjects plus 25% dropout) will have 95% power to reject the above null hypothesis in favor of the alternative assumptions.

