### 7.3 Analysis Methods

Descriptive statistics will be presented for all baseline, procedure and FUP data, as well as device and procedure success, and angiographic endpoints.

For quantitative variables, the mean values, standard deviation, median, maximum and minimum, as well as the 95% CI (confidence interval) for the mean will be calculated. For qualitative variables, absolute and relative frequencies are determined, and the exact 95% confidence interval for proportions is calculated when relevant.

Adverse event rates will refer to the respective time intervals (e.g. 365 +/- 30 days).

Hypothesis testing will be performed for the primary endpoint using one sample one-sided non-inferiority t-test, see section 7.2.

For all clinical secondary endpoints and their components (TLF, cardiac death, all-cause mortality, TV MI, CD TLR, CD TVR, Definite and probable scaffold thrombosis) the survival rate (and 95% CI) will be calculated using Kaplan-Meier estimator. Kaplan-Meier survival curves will also be presented.

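### Rejecting H0 shows mean 6-month late lumen loss below a fixed 0.435 mm, but the protocol reads it as non-inferiority to a historical control whose mean is only estimated

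*Protocol*

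**What the plan says.** Protocol section 4.2 frames the primary question as "non-inferiority of the 6-month in-scaffold late lumen loss of the DREAMS 3G scaffold vs. in-scaffold late lumen loss of a historical control". Section 7.2 builds the control from six published 6-month results: "A weighted mean of 0.29mm for in-scaffold late lumen loss and a weighted pooled SD of 0.34mm were calculated". The control parameter is the "historical control value derived as the weighted mean of in-scaffold LLL at 6" months, set at 0.29 mm, and 0.145 mm "is the prespecified non-inferiority margin". The two are added, so the null hypothesis becomes a mean of at least 0.435 mm. Section 7.3 names the analysis: "Hypothesis testing will be performed for the primary endpoint using one sample one-sided non-inferiority t-test".

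On operating characteristics, section 7.2 states: "A total of 88 subjects enrolled (74 subjects plus 15% dropout) will have 95% power to reject the above null hypothesis", at an alpha of 0.025. On interpretation it states: "Rejection of the null hypothesis will mean that in-scaffold LLL of DREAMS 3G is non inferior to the historical control at 6-month". The 12-month endpoint has the same structure, with 0.33 + 0.145 = 0.475 mm and a parallel sentence: "Rejection of the null hypothesis will mean that in-scaffold LLL of DREAMS 3G is non inferior to the historical control at 12-month". The conclusion of section 7.2 goes further and speaks of enrolling enough subjects to prove non-inferiority against the historical control devices.

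The protocol gives no standard error or interval for the 0.29 mm, and nowhere describes 0.435 mm as a performance goal.

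**The concern.** A one-sample t-test carries the sampling error of the new trial only. It answers whether mean late lumen loss lies below 0.435 mm. The statement that DREAMS 3G is less than 0.145 mm worse than the control devices also depends on where the true control mean lies, and that mean is known only with error. If the pooled estimate happens to be too high, the limit is too lenient for the comparative claim, and the test cannot see this.

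At stake is what a positive primary result may be said to show. Section 4.1 gives CE approval as the purpose of the study, so the meaning attached to rejection matters. The meaning is written into the protocol itself. An additional analysis in a statistical analysis plan would not correct the sentences in section 7.2.

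**Working it through.** **Inputs (protocol section 7.2).** One-sided alpha 0.025; margin 0.145 mm; SD 0.34 mm; 74 evaluable; six control rows as mean (SD), N: 0.44 (0.35), 26; 0.19 (0.18), 41; 0.19 (0.19), 14; 0.44 (0.36), 113; 0.20 (0.32), 113; 0.25 (0.40), 100.

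**1. The plan's own figures.**
- Total N = 407. Weighted mean = Σ N·mean / 407 = 119.21 / 407 = 0.293 mm (stated 0.29).
- Pooled SD = √[Σ(N−1)SD² / Σ(N−1)] = √(46.65 / 401) = 0.341 mm (stated 0.34).
- Exact one-sample t-test power at n = 74 is 0.9515, and at n = 73 it is 0.949, so 74 is right. 74 / 0.85 = 87.06, rounded up to 88.

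Everything reproduces, with 0.29 mm treated as a known constant.

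**2. Standard errors.**
- New trial: SE_t = 0.34 / √74 = 0.0395 mm.
- Control mean, within-study error only: SE_c = √(Σ N·SD²) / 407 = √47.23 / 407 = 0.0169 mm.
- Combined: √(0.0395² + 0.0169²) = 0.0430 mm.

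**3. Error of the comparative claim.** Let the device be truly 0.145 mm worse than the true control mean, and average over the error in the control estimate. The planned test then rejects with probability 1 − Φ(1.96 × SE_t / √(SE_t² + SE_c²)).
- SE_c = 0: 0.025.
- SE_c = 0.0169: 1 − Φ(1.96 × 0.0395 / 0.0430) = 0.036. With the t critical value it is 0.035.

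**4. Power if the test carried the control's error.** At zero true difference, Φ(0.145 / 0.0430 − 1.96) = Φ(1.41) = 0.92. At 86 evaluable (115 less 25%) the same formula gives 0.949, and at 97 (115 less 15%) it gives 0.965.

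**5. Pass limit for the observed mean at n = 74.**
- Planned test: 0.435 − 1.993 × 0.0395 = 0.356 mm.
- With the control's within-study error: 0.435 − 1.96 × 0.0430 = 0.351 mm.

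The first uses the t and the second the normal multiplier. With 1.993 in both, the second is 0.349 mm, so the shift is 0.005 to 0.007 mm.

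**6. A wider scenario: between-study variance added.** The six rows give Cochran Q = 47.3 on 5 df, I² = 89% and a DerSimonian-Laird between-study SD of 0.109 mm.

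| Control SE | mm | One-sided error | Power |
|---|---|---|---|
| Within-study only | 0.0169 | about 0.035 | 92% |
| Random-effects mean | 0.0479 | about 0.10 | 65% |
| N-weighted mean, between-study variance added | 0.0551 | about 0.125 | 57% |

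The last two rows rest on a model that the protocol does not use.

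No error rate was calculated for the 12-month endpoint. The point there rests on its identical structure.

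**The case against.** The strongest reply is that the protocol states its error rates for the null hypothesis as written. It prints every mean, SD and N, substitutes openly, writes the null as a mean of at least 0.435 mm and names a one-sample test. For that null the size is 0.025, and a fixed threshold is a legitimate single-arm design. This stands: there is no arithmetic error, and alpha and power need no correction for the fixed limit. What it does not rescue is the interpretation, because section 7.2 says rejection means, and proves, something about the control devices.

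A reader might infer that the true error is 0.125, five times nominal. The documents do not support that as the headline. It assumes the six studies are exchangeable draws from a population of scaffold studies, and estimates the between-study variance from six rows. The control is a named list of trials, and its spread is mostly a gap between two groups of rows: the four rows at 0.19 to 0.25 mm are homogeneous (Q = 1.66 on 3 df, p = 0.65), and the other two, Magmaris and the first-generation ABSORB, are both at 0.44 mm. For the average of this listed set, within-study error is the relevant quantity. Even under random effects the figure falls to about 0.10 when the random-effects mean replaces the N-weighted one.

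A reader might also fault the SD of 0.34 mm for leaving out the between-study spread. That would be a mistake: a one-sample test needs the subject-level SD within the new trial, and the within-study pooled SD is the right planning value.

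Finally, the practical effect under within-study error is small. That is true, and it limits the weight of the point without removing it.

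**Conclusion.** The point holds as a mismatch between test and conclusion. Rejection shows that mean in-scaffold late lumen loss at 6 months is below 0.435 mm. It does not show non-inferiority to the historical control at the stated 0.025, nor does the 95% power refer to that claim.

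The size that the protocol's own table supports is modest: at 74 evaluable subjects, a one-sided error of about 0.035 instead of 0.025, power of about 92% instead of 95%, and a pass limit of about 0.351 instead of 0.356 mm. This assumes normal errors, SD 0.34 mm, the protocol's sample-size weights, and averaging over the sampling error of the control mean. An error of about 0.10 to 0.125 with power of about 57% to 65% is a scenario under an added exchangeability assumption and should be presented only as that. The change is worth making because it alters what the trial may conclude and costs little.

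**What to change.** Keep the one-sample t-test, the two limits and the sample size.

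1. In protocol sections 4.2, 7.2 and 7.3, state that 0.435 mm at 6 months and 0.475 mm at 12 months are fixed performance goals, that alpha 0.025 and power 95% refer to those goals, and that rejection means mean late lumen loss is below the goal. Change the sentence in the conclusion of section 7.2 about proving non-inferiority in the same way.
2. Prespecify one supportive result: the upper 97.5% confidence limit of the DREAMS 3G mean minus the pooled control mean, with the control's within-study standard error included, compared with 0.145 mm. Use the wording of non-inferiority to the historical control only if this limit is met.
3. Show a random-effects version as a sensitivity analysis, not as a condition. At about 57% to 65% power it would be a poor gate.

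Cost: wording in three sections and one calculation from summary data already printed; no extra patients or procedures. The downside is a slightly weaker comparative claim, with about 92% power at 74 evaluable subjects. If 86 to 97 of the 115 enrolled are evaluable, that power is about 95% to 96.5%, so the planned enrolment largely absorbs the loss.
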